## Abstract

**Background:**

Longitudinal studies of women’s health often seek to identify predictors of good
health. Research has shown that following simple guidelines can halve women’s mortality.
The ongoing Australian Longitudinal Study of Women’s Health (ALSWH) shows that
Australian women are getting better at reducing their smoking and alcohol use, and are
generally diligent about attending recommended health screenings, but are becoming less
successful at dealing with obesity. There are communities of women who live unusually
healthy lives (Rosetans, Seventh-Day Adventists, traditional Japanese women), but their
lifestyles are unlikely to be adopted widely. Universal Medicine (UM) is a
complementary-to-medicine approach that emphasizes personal empowerment and the
importance of menstrual health symptoms.

**Objective:**

This survey investigates whether the approximately 500 women associated with UM exhibit
health status significantly above the norm. As part of this investigation, questions for
a newly developed menstrual attitudes questionnaire will also be evaluated.

**Methods:**

A quantitative cross-sectional survey of women in a UM cohort was designed with the
help of three focus groups of women at three life stages: in menses, peri-menopausal,
and menopausal. The menstrual attitudes portion of the survey incorporates the insights
of these women regarding female health issues. The survey also includes 41 questions
taken from the ALSWH. Focus groups generated additional questions about symptoms
experienced and attitudes toward female health issues. ALSWH questions, including a
range of health scales like the Short Form 36 (SF-36), Center for Epidemiologic Studies
Depression Scale, Perceived Control Scale, Kessler Psychological Distress Scale, and the
Multi-Item Summed Score for Perceived Stress, along with questions about experienced
major health events, were investigated and incorporated if considered suitable. At the
time of publication of this protocol, data collection has been completed.

**Results:**

The validity of the menstrual attitudes questionnaire will be evaluated with Cohen’s
kappa. ALSWH respondents and UM participants will be compared, using unweighted
regression or regression weighted or normalized by age, education, and interest in
alternative treatments (to increase comparability), as appropriate. Analyses will
determine whether UM-related variables (being a UM participant, length of UM
participation, number of UM events attended) are associated with: differences in the
number of major health events and health symptoms experienced; SF-36 physical and mental
health scores; body mass index; and consumption of alcohol, tobacco, sugar, salt,
caffeine, and dairy.

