### Universal Medicine

UM was founded in 1999 by [name], with the stated goal of, “providing
Complementary Health & Healing Services that are Universal in their approach towards
medicine and healing” [23]. Although [name] has
no background in medicine or healing, as of 2015, approximately 200 men and 500 women were
coming regularly to workshops and seeking treatments from UM-accredited practitioners.
[name] describes UM’s mission as follows:

Through practical philosophies that inspire more self-caring and self-loving choices in
daily life, Universal Medicine supports people to explore their overall well-being, the
development of energetic awareness, and the depth they can bring to their quality of
life and relationships [23]

UM teachings are delivered in the form of lectures, audio recordings, and treatments from
UM clinics. Regular courses, workshops, and retreats are conducted throughout Australia
and internationally. Individual participation levels range widely from consuming one or
more webcasts per year to regular physical attendance at events in North Eastern New South
Wales, Australia or in Frome, Somerset, United Kingdom, which receives approximately 700
regular visitors, including a number of health care professionals.

Over time the authors of this paper became aware of the fact that the large majority of
participants in UM appear to lose weight with little or no effort and yet also report
gains in vitality, as evidenced by observations that participants seem to be able to work
or study for longer periods of time. These changes occur despite the fact that neither
weight loss nor increased vitality is ever explicitly considered or targeted during UM
events. Informal surveys have also indicated that very few members of the group eat gluten
or dairy, drink alcohol or smoke, or consume caffeine. These individuals appear to have
less added sugar and salt in their diets than the normal population does, and also seem to
have little or no difficulty maintaining such a diet.

If these observations are accurate, and if the skills and behaviors associated with UM
participants’ dietary choices and weight loss are transferable to the population at large,
then UM holds a key to very substantial decreases in population health expenditure via
reductions in obesity levels and decreased consumption of alcohol and tobacco. UM also
differs from the norm in its attitude toward women’s health. The numerous and varied

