#### The Respondent Population

The respondent population is approximately 500-600 women who, as users of complementary
medical services, may have had a similar profile to women who use alternative
practitioners (ie, more likely to be middle-aged, have poorer health, and a higher usage
of conventional medicine) [42]. On the basis of
some researchers’ observations and informal surveys, the population’s average age is now
in the high 40s, they have lost substantial weight since joining UM activities, and may
have higher than average levels of vitality.

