#### Final Composition of the Study Survey

After consultation with the focus groups, it was decided that all participants would
answer the same selection of questions from the ALSWH, plus the newly developed question
about food. Early versions of the survey were completed by individual members of the
focus groups, and their feedback was incorporated into the survey. When the survey was
nearing its final version, 10 of the focus group members completed it, and their
feedback was also taken into account.

The first section of the survey asks for consent and confirms that the respondent is at
least 18 years of age. Respondents are also asked about the date of their first UM event
and their overall level of participation in UM. This section comprises 4 items. A major
part of the survey for the proposed study is the SF-36 [36] questionnaire, which is also part of the ALSWH. The SF-36 is
used to assess parameters of physical and mental health. In the proposed study, all
items of the SF-36 will be used. Further ALSWH-employed scales used in the survey are
questions from the Center for Epidemiologic Studies Depression Scale [43,44],
Perceived Control Scale [45], Kessler
Psychological Distress Scale [46], and the
Multi-Item Summed Score for Perceived Stress [47].

On the menstrual attitudes section of the survey, menopausal women answer 42 questions,
peri-menopausal women answer 54 questions, and women in menses answer 48 questions.
Those who have never had any periods are invited to answer the menopausal women’s
questions. Women self-select into the group that they think best fits their situation;
however, if after choosing a group, they find that the questions do not appear to apply
to them, they can back out of the survey and choose a different group.

The first set of questions consists of a list of symptoms with a response scale
including *Yes*, *definitely/Yes*,
*sometimes/No*, *not much/No*, and *not at
all*, which is the same as that in the widely used Women’s Health
Questionnaire [48]. This response scale was
adopted after several more complicated response schemes were tried and discarded to
reduce satisficing [49]. The survey contains
24, 26, and 26 menopausal, peri-menopausal, and menses symptom questions, respectively
(of which 13 are common to all three groups). The survey also contains 24, 29, and 16
menstrual attitude questions, respectively (of which one is common to all three groups

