### Summary Analysis

Key indicators of health and comparisons of those indicators to ALSWH statistics (where
available) that this survey aims to measure are: (1) SF-36 physical and mental health
scores; (2) BMI; (3) symptoms experienced over the previous 12 months; (4) consumption of
alcohol, tobacco, sugar, salt, caffeine, and dairy; and (5) prevalence and levels of
depression, stress, distress, and perceived control, as measured by standard scales.

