### Comparative and Detailed Analyses

Comparisons between UM participants and ALSWH respondents are planned, using both simple
comparisons and comparisons weighted or normalized by age, education, and interest in
alternative treatments (to increase comparability).

Regression analyses will be performed to determine whether SF-36 scores or BMI are
associated with: (1) UM-related variables (length of UM participation, number of UM
events); (2) demographic variables (age, age of menopause, age of menarche, education
history); (3) menstruation-related attitudes and symptoms; (4) frequency of health-related
symptoms; (5) major health events experienced; (6) alcohol and tobacco consumption; (7)
sugar, salt, dairy, and caffeine consumption; (8) frequency of medical and other health
practitioner visits; or (9) scores on other standardized scales (depression, perceived
control, psychological distress, perceived stress), all of which are derived from the
questions taken from the ALSWH questionnaires.

The expected sample sizes are relatively small (200-400 respondents per item, given that
all items are optional), so any odds ratios and regression coefficients will be considered
significant if their 95% confidence intervals exclude 1.0 (for odds ratios) or 0.0 (for
regression coefficients).

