### Issues with the SF-36 Instrument

The scoring instructions used by the ALSWH for the SF-36 will be employed [60]. The SF-36 physical and mental health summary
scores are normalized to a mean of 50 and a standard deviation of 10. However, giving
perfect answers to every question leads to a physical score on this questionnaire of only
56.5, and a mental score of only 62.5 (for this mental score one would, for example, need
to tick *none of the time* in response to, “How often during the past four
weeks did you feel tired?”).

A further SF-36 scoring feature is that to some extent, mental and physical health scores
are mutually inhibiting. Physical health items are added as a negative score to the mental
health score and mental health items are added as a negative score to the physical health
score. This means that achievement of mental scores above 62.5 is only possible for people
with less than perfect physical health and vice versa. The best theoretically possible
mental health score can only be achieved by a person with very bad physical health and
vice versa. This may affect the usefulness of the SF-36 if many respondents actually have
a high level of both physical and mental health. One question is whether there will be a
ceiling effect, with many scores near the surprisingly low upper limits of the SF-36.

The dose-response approach proposed here uses length of association and number of events
or visits as the estimator of the UM *dose*. If results of the proposed
study suggest that this group is worth investigating further, then in a longitudinal
study, UM participants could be surveyed–perhaps in combination with objective health
measures–at or near the beginning of their association with UM, and at designated
follow-up intervals.

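### Major health events are to be related to the amount of UM participation, but the count is not limited to time after a woman's first UM event

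*Protocol article*

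**What the plan says.** The Results paragraph of the abstract pairs three UM variables with a set of outcomes. It asks whether being a participant, length of "participation, number of UM events attended) are associated with: differences in the" "number of major health events and health symptoms experienced; SF-36 physical and mental" scores and further measures. The section on issues with the SF-36 describes the intent: the "dose-response approach proposed here uses length of association and number of events" or visits to estimate the UM dose.

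The article gives no time window for major health events. Symptoms do have one: Summary Analysis lists "symptoms experienced over the previous 12 months". The Design section and the data-availability statement refer to partial medical history and to lists of procedures and major illnesses, which suggests a history count but does not define one.

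The date needed to separate the periods is collected: "Respondents are also asked about the date of their first UM event" (Final Composition of the Study Survey). The article states no use of it to split events into before and after joining.

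The role of major health events also differs between sections. In the abstract they are an outcome. In Comparative and Detailed Analyses, "major health events experienced; (6) alcohol and tobacco consumption" stand in the list of explanatory variables for SF-36 scores or BMI. The five key indicators in Summary Analysis do not include them.

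**The concern.** A dose cannot act on events that happened before it. SF-36 scores and BMI are measured at the survey, after joining, but a cumulative event count can reach back decades before a woman's first contact with UM. Two things follow.

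- **Dilution.** The years before joining add events that UM cannot have influenced, so any true association is pulled towards no difference.
- **Selection on earlier health.** The Respondent Population section says these women may resemble users of alternative "practitioners (ie, more likely to be middle-aged, have poorer health, and a higher usage" of conventional medicine. A serious illness may be the reason a woman joined. It would then count as an outcome of UM, although it came first. A healthy past would work the other way.

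The Objectives section uses these data to decide whether UM merits further investigation. An event result made up largely of time before joining informs that decision poorly.

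**Working it through.** The article states no event rate, power or sample-size figure on this point, so there is nothing to reproduce. The check is person-time arithmetic.

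**Inputs from the article.** UM founded in 1999 (Universal Medicine). Mean age in the late 40s (Survey Development and Administration); 45, 48 and 50 are used. Expected 200 to 400 respondents per item (Comparative and Detailed Analyses).

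**Assumptions.** Survey in 2015 (ethics approval is dated June 2015). Cumulative event items. Adult window from age 18. Constant event rate apart from any UM effect.

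**Step 1: share of the window before UM.** The longest possible exposure is 2015 - 1999 = 16 years. For a founding member the share is 1 - 16/(age - 18) of adult life, or 1 - 16/age of lifetime.

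- Age 45: 1 - 16/27 = 41% adult; 1 - 16/45 = 64% lifetime.
- Age 48: 1 - 16/30 = 47% adult; 1 - 16/48 = 67% lifetime.
- Age 50: 1 - 16/32 = 50% adult; 1 - 16/50 = 68% lifetime.

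These are minimum shares at each age, because every later joiner has less time in UM.

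**Step 2: dilution.** With window T, years in UM L and true rate ratio RR after joining, the apparent ratio is ((T - L) + RR × L)/T. For a woman aged 48 with T = 30 adult years:

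| Years in UM (L) | Share before UM | Apparent ratio if RR = 0.5 | Apparent ratio if RR = 0.7 |
|---|---|---|---|
| 5 | 25/30 = 83% | (25 + 2.5)/30 = 0.92 | (25 + 3.5)/30 = 0.95 |
| 8 | 22/30 = 73% | (22 + 4)/30 = 0.87 | (22 + 5.6)/30 = 0.92 |
| 16 | 14/30 = 47% | (14 + 8)/30 = 0.73 | (14 + 11.2)/30 = 0.84 |

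With a lifetime window (T = 48) the ratios are closer to 1. For RR = 0.5 they are 0.95, 0.92 and 0.83 in the same order.

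**Step 3: false association through age.** Older women have had more time for events and may have been in UM longer. A simulation with no UM effect regressed a lifetime event count on length of participation (1,000 runs per setting; assumed age SD 10, length mean 8 and SD 4 years, 0.05 events per year). With an assumed age-length correlation of 0.3 to 0.5, the unadjusted test at 5% rejected in 26% to 60% of runs at n = 200 and 46% to 86% at n = 400. With age in the model it rejected in about 4% to 7%. Age adjustment therefore removes this part, but neither the dilution in Step 2 nor selection on illness before joining.

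**Step 4: symptoms.** The 12-month window reaches back before UM only for women who joined in the past year. If joining had been uniform over 16 years (an assumption), that is 1/16 = 6% of women, and 0.5/16 = 3% of total window time.

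**The case against.** The strongest objection is that the article nowhere says the event items are lifetime or adult counts. The survey is in Multimedia Appendix 2, which is not shown, and ALSWH wording was kept where possible, so a short recall window may exist at item level. This stands as a limit: the percentages above hold only if the items are cumulative. It does not remove the point, because the article makes the count an outcome of a dose and gives it no window.

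A second objection is that the article claims association only. The abstract's Conclusions and the Objectives leave causation to later work, and the Discussion leaves the sequence of events to a longitudinal study. This also stands in part. A reader might infer that the event result cannot answer the study question at all. The documents do not support that: the main question is whether UM women have a better health profile than ALSWH respondents, and a history count taken the same way in both groups can describe that. The dose-response use within the UM group is what fails.

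Third, ALSWH women have no joining date, so a post-joining count has no counterpart in the comparator. This is correct, and the two analyses need different remedies.

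Fourth, major events are an outcome only in the abstract. That is also correct, and limits the weight of the point.

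**Conclusion.** The point holds for major health events in the analyses of length of participation and number of UM events. If the items are cumulative and the survey ran in 2015, at least 41% to 50% of adult life (64% to 68% of lifetime) precedes UM for women aged 45 to 50, and 83% of adult life for a 48-year-old with an assumed five years in UM. The association would be diluted and mixed with health before joining.

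Two stronger readings are tempting but unsupported. A reader might infer that any UM effect vanishes; for a founding member aged 48 a true ratio of 0.5 would still show as 0.73 over an adult window. A reader might also extend the criticism to symptoms, but their fixed 12-month window is affected only for the most recent joiners, about 6% of women under uniform joining.

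**What to change.** Data collection is complete, so the changes are to the analysis and its wording.

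1. **Within the UM group:** count only events after the recorded date of first UM event, with years since that date as person-time and adjustment for age. If events cannot be dated, remove the count from the outcomes tested against UM dose and report it as descriptive health history.
2. **UM versus ALSWH:** use the same event window in both groups, state it, adjust for age, and present the result as a description of health history, not as an outcome of UM.
3. **Symptoms:** add a sensitivity analysis that excludes women whose first UM event was less than 12 months before the survey.
4. **Reconcile the role of major events** between the abstract (outcome) and Comparative and Detailed Analyses (explanatory variable). If they remain explanatory, the date still matters: an event before joining may be a confounder, and one after joining may lie on the pathway from UM to SF-36 or BMI.

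The cost is a derived variable and some rewording, with fewer events and wider intervals in the within-UM analyses. If events were recorded without dates, one outcome named in the abstract becomes descriptive.

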**Conclusions:**

If women in the UM cohort are truly in substantially better health than the norm,
further investigations may be worthwhile to see whether UM plays a causal role, and
whether the women’s practices are generalizable.

**International Registered Report Identifier (IRRID):**

DERR1-10.2196/7993

## Introduction

Various behavioral dimensions are strong predictors of health for both women and men. One
study identified seven behaviors as being of health significance in a cohort of 6928
46-to-70-year-old people from Alameda county (near San Francisco, California) who were
followed from 1965 to 1984: (1) not smoking; (2) using alcohol moderately (if at all); (3)
exercising at least moderately; (4) sleeping 7 to 8 hours each 24-hours; (5) maintaining
moderate weight; (6) eating regular meals; and (7) eating breakfast [1,2]. Respondents who reported
performing six or seven of these behaviors had less than half the mortality, and those who
performed four or five of the behaviors had approximately two-thirds the mortality, compared
with those who performed fewer than three [1,2].

### Exemplary Populations

There are groups of people who have been documented as having unusually healthy profiles,
including the inhabitants of the small American town of Roseto, Pennsylvania [3], Seventh-Day Adventists [4], Japanese living a traditional Japanese lifestyle [5], and senior Whitehall (United Kingdom) civil
servants [6].

In Roseto, people were living according to traditional Italian roles, where residents
tended to have very strong community ties. The diet of this population was nutritionally
poor, and many did hard and dangerous work in a slate quarry, but their heart disease
morbidity and mortality were much lower than those of inhabitants of surrounding towns
[3]. Seventh-Day Adventists have lower coronary
heart disease rates and lower rates of many cancers, among other health indicators, but
they are a traditionalist Christian offshoot with strict rules [4]. Strict hierarchies were, and are, an important feature of Japanese
life [7]. The better health of high-level British
public servants may simply be evidence that those with better general habits are better
able rise to higher positions [6]. Therefore, none
of these four groups is without its limitations in terms of producing lifestyles that the
general population would be likely to embrace.

### Women-Specific Research

A 1999 report that investigated the inclusion of women in various types of medical
research found that in nongender-specific research, women were vastly underrepresented as
research subjects [8]. Rodin and colleagues [9] have contributed significantly to the understanding
of women’s health concerns, which differ from those of men. These researchers described
women-specific health concerns such as hysterectomy, dysmenorrhea, caesarean section,
almost all incidences of breast cancer, and some concerns not exclusively (but primarily)
relevant to women, such as rheumatoid arthritis, lupus, osteoporosis, and eating disorders
[9]. It has also been documented that 70% of
psychoactive medications (eg, antidepressants, tranquilizers) are prescribed to women
[10], and two-thirds of all surgeries are
performed on women [11].

Measuring and improving female health is an important task for many governments,
particularly those that have aging populations, and in which the incidence and prevalence
of illness and disease are rising sharply. Unfortunately, this is a widespread problem:
the rates of large-scale health issues like obesity and diabetes are rising [12,13]. The
associated rise in health care costs adds to the urgency of this problem [14].

In Australia, the Australian Longitudinal Study on Women’s Health (ALSWH), with 58,000
women, was inaugurated in 1986 and added a further 17,000 women aged 18-23 years in
2012/2013. The purpose of the ALSWH is to, “clarify cause-and-effect relationships between
women's health and a range of biological, psychological, social, and lifestyle factors”
[15]; hence, this study’s data holds promise
for elucidating predictors of good health in women.

